## Abstract

Although several interventions that target obesity have been examined, the success of these interventions in generating and maintaining positive results has yet to be confirmed. This study protocol therefore presents a trial aimed at analyzing the effectiveness of a well-being-centered acceptance and commitment therapy (ACT)- and mindfulness-based group intervention following the valued-based healthy living (VHL) approach (Mind&Life intervention) for individuals experiencing overweight-related distress. A randomized controlled trial with two parallel groups will be conducted in 110 adults attending primary care units with overweight or obesity. Participants will be randomly allocated to one of the two study conditions. Interventions will either be the treatment as usual (TAU) or the Mind&Life intervention—an ACT- and mindfulness-based intervention—plus the TAU intervention. Quality of life, weight self-stigma, general health status, eating habits, physical activity, eating behavior, anthropometric, body composition, cardiovascular, and physiological variables, as well as process variables, will be examined at baseline, posttreatment, 6-month follow-up, and 1-year follow-up. This trial aims to offer a novel psychological approach for addressing the psychological and physical impairments suffered by people with overweight or obesity in the current environment. ClinicalTrials.gov identifier: NCT03718728.

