##### Sample Size

Sample size and power estimation were calculated for 5% alpha error, a 2-tailed test, and 80% statistical power (beta error = 20%). The trial uses a comparison group and experimental group design for which pretreatment–posttreatment differences are expected to have an effect size of 0.68 (Cohen’s *d*) for quality-of-life index. The latter has been elected due to the VHL approach of Mind&Life intervention, since among all primary outcomes, quality-of-life index could best reflect values’ work impact. This effect size is based on that of a previous trial studying an acceptance, mindfulness, and compassion-based group intervention program for people struggling with weight-related issues [44]. Since dropout rates of 4–20% have previously been observed, in the present trial, the sample size and statistical power calculations are based on a 20% attrition rate. Hence, it is estimated that 55 participants per group (110 in total) will be needed to evaluate one of the main outcomes of the study, that is, quality of life.

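### The stated sample-size inputs give 44 per arm (88 in total), not the stated 55 per arm (110); the discrepancy is conservative, but the basis of 110 is not reproducible

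*Protocol article*

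**What the plan says.** The Sample Size section (2.3.2) of the protocol article sets out the calculation in full. It specifies a 5% alpha error, "a 2-tailed test" and 80% power. It describes the design thus: "The trial uses a comparison group and experimental group design". For the quality-of-life index it states that "pretreatment–posttreatment differences are expected to have an effect size of 0.68", on Cohen's d scale, taken from a previous trial of a related group programme. On losses it says that "the sample size and statistical power calculations are based on a 20% attrition rate". From these inputs it draws its result: "it is estimated that 55 participants per group (110 in total) will be needed".

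The Abstract repeats the total: "A randomized controlled trial with two parallel groups will be conducted in 110 adults". Sections 2.1 and 2.5 give 1:1 allocation. Section 2.10 (Data Analysis) plans ANOVA and/or ANCOVA with group as the factor, and judges each test at p ≤ 0.05.

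**The concern.** The section states everything that a two-group comparison of means needs and presents 55 per arm as the consequence. This is therefore not a detail left to a fuller document: the article gives a derivation and a result, and the two can be checked against each other. They disagree by more than rounding or the choice of formula can explain.

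The number randomised and the power are the two figures that a funder, ethics committee or later reader takes from this section. If they do not belong together, the reader cannot tell what power the trial was planned to have, for what effect, or whether the additional participants are a deliberate allowance or a slip.

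**Working it through.** **Inputs**, from section 2.3.2 unless noted: two-sided alpha 0.05; power 0.80; d = 0.68 (standardised, so SD = 1); attrition 20%; two groups, 1:1 (sections 2.1 and 2.5).

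**Step 1. Evaluable participants per arm.**

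- Normal approximation: n = 2(z₀.₉₇₅ + z₀.₈₀)²/d² = 2(1.960 + 0.842)²/0.68² = 2 × 7.849/0.4624 = 33.9, so 34.
- Two-sample t-test (noncentral t): n = 34.94, so 35. Power at 35 per arm is 80.1%.

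**Step 2. Attrition.** Randomised = n/(1 − 0.20).

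- t-test: 35/0.80 = 43.75, so 44 per arm, 88 in total.
- Normal approximation: 34/0.80 = 42.5, so 43 per arm, 86 in total.

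**Step 3. Attempts to reproduce 55 with other conventions, keeping alpha 5%, power 80% and d = 0.68.**

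| Variant | Evaluable per arm | Randomised per arm |
|---|---|---|
| t-test, n/(1 − 0.20) | 35 | 44 |
| t-test, n × 1.20 | 35 | 42 |
| Normal approximation, n/(1 − 0.20) | 34 | 43 |
| Normal approximation, n × 1.20 | 34 | 41 |
| One-sided t-test, n/(1 − 0.20) | 28 | 35 |
| Rank test, efficiency 0.955 to 0.864, n/(1 − 0.20) | 37 to 41 | 47 to 52 |

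A paired calculation needs 19 before attrition. None of these reaches 55. The ANCOVA option in section 2.10 does not explain the gap either, because a useful covariate reduces residual variance and so lowers the requirement.

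**Step 4. What would give 55.** Applying the allowance twice: 35/0.80 = 43.75, so 44; then 44/0.80 = 55 exactly. Inputs that the section does not state also reach or approach 55:

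- d = 0.61 with 20% attrition: 44 evaluable, 44/0.80 = 55.
- 90% power, normal approximation, n × 1.20: 45.45 × 1.20 = 54.5, so 55. With the t-test, 90% power needs 47 evaluable, which gives 57 by n × 1.20 or 59 by n/(1 − 0.20).
- Alpha 0.025 with attrition: 43/0.80 = 53.75, so 54.
- Alpha 0.05/6 with no attrition: 55.
- A clustering allowance on both arms with groups of 14 and an assumed ICC of 0.02: design effect 1 + 13 × 0.02 = 1.26, and 35 × 1.26/0.80 = 55.1. Over assumed ICCs of 0.01 to 0.05 the same formula runs from 49.4 to 72.2, so the match depends on the ICC chosen.

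**Step 5. What 55 per arm delivers.** 55 × 0.80 = 44 evaluable per arm.

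- Power at d = 0.68 with 44 per arm: 88.4%.
- Effect detectable with 80% power at 44 per arm: d = 0.604.
- With no attrition (55 evaluable per arm): 94.2% power at d = 0.68.

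**Size of the gap:** 55 − 44 = 11 per arm, 22 in total, and 22/88 = 25%.

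**The case against.** The strongest reply is that the discrepancy is harmless. The plan asks for 80% power and, on its own assumptions, enrols enough for about 88%. No analysis and no enrolment figure has to change; only the explanation of the number does. That is right, and it limits the weight of the point. What it leaves standing is that 22 participants have no stated justification and that the 80% power in the text does not describe the trial as sized.

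The second reply is that an undisclosed but sensible input may lie behind 55. This cannot be excluded, as the alternatives in the working show. But the section mentions no higher power, smaller effect, multiplicity correction or clustering allowance. It states 80% power and d = 0.68, and section 2.10 tests each outcome at 0.05, so several of those routes contradict the text as it stands.

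Three stronger readings are tempting and the document does not support them:

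- **That the attrition allowance was applied twice.** The exact match is suggestive, but no intermediate figure is shown and other routes also arrive at 55. It is one possible cause.
- **That 0.68 is a within-arm change and so the wrong parameter.** The sentence ties the effect to a two-group design, and its natural reading is a between-group effect on change. Settling it would need the cited trial, which is not at hand.
- **That the surplus was meant to cover clustering in the therapy groups.** Section 2.4.2 gives groups of 12 to 14, but the Sample Size section gives no ICC and no design effect.

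**Conclusion.** The point holds as a discrepancy between stated inputs and stated result. Two-sided 5% alpha, 80% power, d = 0.68, 20% attrition and 1:1 allocation require 44 randomised per arm (88 in total), or 43 per arm by the normal approximation. The stated 55 per arm (110) is 25% above 88 and cannot be reproduced from these inputs.

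A reader might infer that the trial is underpowered. The calculation shows the opposite on the plan's own assumptions: the error, if it is one, is on the safe side. The power of 88% at d = 0.68, and the detectable effect of about 0.60 at 80% power, assume independent observations, a standard two-sample comparison and losses of exactly 20% in each arm.

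Confidence is high for 88 against 110. The cause of the gap remains unknown.

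**What to change.** Keep 110 and correct the justification in one of two ways.

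1. If no further input was intended, restate the basis. For example: 35 evaluable participants per arm give 80% power for d = 0.68 at two-sided 5%, which is 44 randomised per arm with 20% attrition. The trial will randomise 55 per arm; with 20% attrition, 44 per arm remain, giving about 88% power for d = 0.68, or 80% power for d of about 0.60, assuming independent observations.
2. If 55 came from a further input, such as a smaller effect, higher power or a clustering allowance, state that input and its value so that the figure can be reproduced.

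The cost is the rewording of one paragraph. The total in the Abstract stands, and enrolment does not change.

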### 2.4. Interventions

Eligible participants will be randomly allocated to either the Mind&Life or the TAU intervention, both of which are of 5 months duration.

#### 2.4.1. Treatment as Usual

This intervention consists of 5 monthly individual sessions of 30 min and includes nutritional advice and recommendations for physical activity. The sessions will be delivered by a nutritionist and will take place in a laboratory of the Faculty of Psychology of UPV/EHU. All sessions will follow the same structure. First, the participant’s anthropometric measures will be taken, after which their physical state and progress during the last month will be examined. The dietetic and physical activity registration form will then be reviewed. Finally, the nutritionist will provide information about a specific topic. An overview of the content of each session is displayed in Table 1. Participants will be provided with a folder with their initial anthropometric assessment report and session materials, as well as a card and a pen to note down the measures taken at each session. They will also be asked to keep a record of daily dietary habits and physical activity, which will be reviewed in each session.

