### 2.8. Data Collection and Assessment Plans

For the present trial, the outcomes will be measured at baseline, posttreatment, 6-month follow-up, and 1-year follow-up. Weight, body fat percentage, waist and hip circumference, and blood pressure will also be measured monthly during the intervention period (see Figure 1 for details of the assessment schedule). Self-reported measures will be collected using the *Encuesta Fácil* online platform (www.encuestafacil.com). Assessment sessions will take place in a computer room and a laboratory in the Faculty of Psychology at UPV/EHU, located in Donostia-San Sebastian. Blood samples will be collected by a nurse in each participant’s primary care unit. A nutritionist will be responsible for evaluating anthropometric and dietetic aspects, having been trained specifically for that task. A psychologist will be in charge of conducting the assessment sessions for the other variables evaluated in the study, having also been trained for that purpose. The evaluated outcomes and the properties of the assessment instruments to be used are detailed below.

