### 2.10. Data Analysis

Primary, secondary and process-outcomes will be analyzed using the statistical program SPSS version 26.0 for Windows (IBM Corp., Armonk, NY, USA). Taking into account the aims of the study, the effects of the Mind&Life program will be examined by analysis of variance (ANOVA) and/or covariance analysis (ANCOVA), with group as the independent or fixed variable (experimental or control) and all study outcomes as dependent variables. If any difference in relation to a variable exists at baseline, it will be introduced as a covariate in the analyses. Likewise, when making comparisons at follow-up points (6-month and 1-year follow-up), pretreatment–posttreatment changes will also be introduced in the analyses as covariates. To estimate effect sizes, Cohen’s *d* will be calculated where values between 0.2 and 0.4 will indicate small effects; between 0.5 and 0.7, medium effects; and above 0.8, large effects [70]. Additionally, we will use multiple regression in order to predict the variables that best explain changes in the quality-of-life criterion variable. For mediation and moderation analyses, AMOS software will be used. For each test, values of *p* ≤ 0.05 will be considered significant.

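### Weight, body composition and blood pressure are measured monthly in both arms, but the stated posttreatment analysis of these secondary outcomes gives the monthly values no role

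*Protocol article*

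**What the plan says.** - **Measurement.** Section 2.8 states: "Weight, body fat percentage, waist and hip circumference, and blood pressure will also be measured monthly during the intervention period". Section 2.4.1 says of TAU: "This intervention consists of 5 monthly individual sessions of 30 min". It also says that at each session "anthropometric measures will be taken, after which their physical state and progress during the last month will be examined". That last sentence describes how a session runs, not the analysis; section 2.8 is the firmer source for the data collected.
- **Both arms.** The Abstract describes the experimental condition as "an ACT- and mindfulness-based intervention—plus the TAU intervention", and the aims in the Introduction say the same. The monthly record therefore exists in both arms.
- **Time points.** According to the Abstract, the outcomes "will be examined at baseline, posttreatment, 6-month follow-up, and 1-year follow-up".
- **Analysis.** Under section 2.10 the effects of the programme "will be examined by analysis of variance (ANOVA) and/or covariance analysis (ANCOVA), with group as the independent or fixed variable", with every study outcome as a dependent variable. The section names no repeated-measures model and no use of the monthly values.
- **Attrition.** The sample size and power calculations are "based on a 20% attrition rate"; earlier drop-out is given as 4–20%.

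**The concern.** A comparison of posttreatment values by ANOVA or ANCOVA uses only participants who have a posttreatment value, unless something is imputed. Someone who leaves in the third month has several recorded weights, and these say a good deal about where that person was heading, yet the named method has no place for them. Analysing the four main visits jointly would not help at posttreatment, because a person lost during treatment has only the baseline among those four.

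At stake is the posttreatment part of the secondary goal for weight (hence BMI), body fat percentage, waist, hip and blood pressure. Precision is lost, and the estimate can be biased if leaving depends on how weight is changing, above all if it does so more in one arm. This is conceivable here: participants seek weight management and review their progress monthly, and only one arm has the 15 group sessions that de-emphasise weight. The article gives no data on it.

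**Working it through.** **The plan's own figure.** For d = 0.68, two-sided 5% and 80% power, the t-test needs 35 per arm; 35 / 0.8 = 43.75, so 44 after 20% attrition. The stated 55 is not reproduced, but it is larger than needed. That is a separate matter. Only the 55 per arm and the 20% are used here.

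**Participants concerned.** 55 × 0.20 = 11 per arm without a posttreatment value, leaving 44. This is an upper figure, since some attrition may come after posttreatment. At 4%: 55 × 0.04 = 2.2 per arm.

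**Precision, by formula.** Let *d* be the drop-out proportion and *r* the correlation, given arm and baseline, between the last monthly and the posttreatment value (assumed; the article gives none). If the lost participants have that last monthly value, the variance relative to completers only is about 1 − *d r*². The effective size per arm is then 55(1 − *d*) / (1 − *d r*²):

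| *d* | *r* | Effective n per arm |
|---|---|---|
| 20% | 0.7 | 44 / 0.902 = 48.8 |
| 20% | 0.8 | 44 / 0.872 = 50.5 |
| 20% | 0.9 | 44 / 0.838 = 52.5 |
| 20% | 0.95 | 44 / 0.8195 = 53.7 |
| 4% | 0.7 to 0.95 | 53.9 to 54.8 (from 52.8) |

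People who leave early have only an early, less predictive value, so these are upper limits.

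**Bias, first simulation.** Assumptions: 55 per arm, five monthly values, SD of weight change rising to 5 kg at month 5, correlation 0.9 between adjacent months, true difference −2.0 kg, and drop-out after months 1–4 depending on the last observed change.

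| Drop-out depends on weight change | Drop-out | Completers | With monthly values |
|---|---|---|---|
| Not at all | 20% | −2.00 (SE 1.058) | −2.00 (SE 0.982) |
| Both arms, log-odds 0.2 per kg | 22% | −1.90 | −2.02 |
| Both arms, 0.3 per kg | 24% | −1.76 | −1.98 |
| TAU only, 0.3 per kg | 24% | −0.91 | −1.97 |

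With unrelated drop-out, 1 − 0.982/1.058 = 7% off the standard error.

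**Bias, second simulation.** The true difference is −1.0 kg (mean slopes −0.5 and −0.7 kg/month over five months), with visit-level SD 0.8 kg in the linear courses. Here the spread of individual courses is varied. Entries are completers-only estimates in kg.

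| Individual courses | Both arms, 0.5 per kg | TAU only, 0.3 | TAU only, 0.5 | Range over the drop-out settings in a further run |
|---|---|---|---|---|
| Linear, slope SD 0.8 kg/month | −0.85 | −0.47 | −0.21 | +0.04 to −0.95 |
| Linear, slope SD 0.4 kg/month | −0.93 | −0.90 | −0.82 | −0.71 to −0.98 |
| Random walk | −0.92 | −0.88 | −0.85 | −0.75 to about −1.0 |

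The estimate with monthly values stayed near −1.0 kg throughout. Under random drop-out the standard error fell from 0.86 to 0.80 (7%), 0.48 to 0.45 (6%) and 0.39 to 0.38 (3%, where two-decimal rounding matters). Across all runs the reduction is about 4–7%, with single runs at 3% and 8%.

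**Why the first row is extreme.** With slope SD 0.8, the month-4 to month-5 correlation is 20(0.64) / √[(16·0.64 + 0.64)(25·0.64 + 0.64)] = 12.8 / √(10.88 × 16.64) = 0.95. With slope SD 0.4 it is 3.2 / √(3.2 × 4.64) = 0.83.

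**The case against.** **Nothing says that drop-outs are excluded.** A reader might infer that participants who leave early contribute nothing, or that only four visits will ever be analysed. The documents do not support either as fact. The Abstract lists four time points without excluding others, and section 2.10 names neither an analysis set nor a rule for missing values. Such a rule is commonly left to a full protocol or analysis plan that is not shown, and imputation from the monthly values is not ruled out. This stands, and the point is therefore conditional. What remains is that a method is stated, and as stated it makes no use of data that the same article says will be collected.

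**Attrition is not ignored.** Section 2.6 plans to compare results by attendance and attrition. True, but that comparison does not bring the partial courses into the estimate.

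**The size rests on assumptions.** This stands. Near-total loss of the effect needs widely spread linear courses together with weight-related drop-out in TAU alone. The article gives neither a variance nor a drop-out pattern, so a claim that the effect would largely vanish is not supported.

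**The model can be overbuilt.** This also stands. With baseline, five monthly values, posttreatment and two follow-ups there are nine occasions, and an unstructured covariance has 9 × 10 / 2 = 45 parameters for 110 participants. A random slope running through treatment and a year of follow-up would sit badly with the weight regain described in the Introduction. The model should therefore stop at posttreatment.

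**Conclusion.** The point holds in conditional form and for secondary outcomes only. Monthly values of weight, body fat percentage, waist, hip and blood pressure exist in both arms, and the stated ANOVA/ANCOVA gives them no role. Without imputation, up to 11 per arm would leave the posttreatment comparison at 20% attrition, and about 2 per arm at 4%.

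The certain gain is modest: a standard error about 4–7% smaller at about 20% random drop-out, under assumed variances. The possible gain is protection from bias where drop-out follows the observed course. That bias runs from negligible to large, and the documents do not allow it to be placed within that range. If drop-out is unrelated to weight course, only the precision gain remains.

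The questionnaire and dietary primary outcomes have no monthly values, nor do the blood measures, so this point does not touch them. It lies between a suggestion to consider and a change that should be made. The low cost is the main argument for making it.

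**What to change.** In section 2.10, for weight, BMI, body fat percentage, waist, hip and blood pressure only:

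- Estimate the posttreatment arm difference from a likelihood-based repeated-measures model using baseline, the monthly treatment-period values and posttreatment.
- Include arm, time as a categorical factor, and arm-by-time. Use an unstructured covariance and pre-specify a simpler structure in case it does not converge. With seven occasions that is 7 × 8 / 2 = 28 covariance parameters, fewer if a monthly session coincides with a main visit.
- Include all randomised participants with any post-baseline value, and report the arm difference at posttreatment. Do not test the arms month by month.
- Do not impose a random slope that spans both treatment and follow-up.

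**Cost.** A few sentences and somewhat more modelling; SPSS, already named, fits such models. No new visits, data or participants. The analysis relies on missing-at-random given the monthly values, which is weaker than what a completers-only comparison requires. Anyone lost before the first monthly value is still not recovered.

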#### 2.4.2. Mind&Life Intervention

This group intervention is a combination of ACT- and mindfulness-based intervention following a VHL approach centering primarily on valued living. It consists of 15 two-hour sessions, the first 10 being held weekly and the last 5 being held biweekly. At the end of the treatment, the participants will be followed up with a monthly telephone call for a period of 6 months in order to review personal values, value-driven behaviors, and the integration of mindfulness into their everyday life [48]. The intervention has been developed by consulting ACT manuals [49,50], including those that specifically target weight loss [51,52], an ACT metaphor and exercises book [53], along with a mindfulness [54] and mindful eating [55] exercise book. Moreover, Kg-Free [44] has been taken as reference for the elaboration of Mind&Life intervention, although there are significant differences in participants’ inclusion criteria (e.g., age and gender), follow-up length, and intervention components (e.g., compassion’s presence, values revising frequency or mindfulness practice). Two psychologists with training in third-wave therapies will be responsible for conducting the sessions in small groups (from 12 to 14 participants), which will take place in a classroom of the Faculty of Psychology of UPV/EHU where chairs will be arranged in a circle. The Mind&Life intervention is characterized by avoiding overemphasis on weight loss during the whole intervention process. Instead, the intervention targets psychological well-being by clarifying personal values and fostering value-driven behaviors. Whereas reflecting on the personal values that underpin self-care will be of great importance, the interventionists will take care to prevent the participants from basing their personal development on weight-related aims. All sessions will follow a common structure: Mindfulness practice (general or mindful eating), an explanation of the session content with the use of metaphors or experiential exercises, and an explanation of homework tasks. The specific components of each session are presented in Table 2. Participants will be supplied with a manual containing a summary of each session, homework instructions, and contact information. Further, at the end of each session, the interventionists will send participants an audio file with the mindfulness exercise in order to facilitate daily practice. Additionally, they will be asked to record their daily mindfulness practice in either paper or online format.

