### 2.5. Randomization

Participants will be randomly assigned to either the experimental or the comparison group using a 1:1 allocation ratio. Blocked randomization will be used, and a computerized random sequence generator (www.random.org) will determine the sequence of each block. First, the size of the block will be established, after which a member of the research team not involved in the assessment sessions or the delivery of the treatment will write down the allocation sequence of each block on a sheet of paper which will be concealed in an opaque, sealed envelope. At the time of allocation, once participants have provided consent, the research team member in charge of the assessments and delivery of the treatment will open the corresponding envelope to reveal the allocation sequence to assign each participant to the corresponding group.

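### Mind&Life is delivered in therapy groups and TAU individually, but the planned ANOVA/ANCOVA and the sample size ignore clustering; the test is anti-conservative if outcomes within a therapy group are positively correlated

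*Protocol article*

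**What the plan says.** Randomisation is of individuals, 1:1 in blocks (Section 2.5). Delivery then differs by arm:

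- **Mind&Life (Section 2.4.2):** 15 two-hour group sessions. Two psychologists "will be responsible for conducting the sessions in small groups (from 12 to 14 participants").
- **TAU (Section 2.4.1):** "This intervention consists of 5 monthly individual sessions of 30 min", given by a nutritionist. The experimental arm receives TAU as well (Abstract and Introduction), so the therapy groups are a feature of one arm only.

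Section 2.10 states that the effects "will be examined by analysis of variance (ANOVA) and/or covariance analysis (ANCOVA), with group as the independent or fixed variable". The parenthesis that follows defines this factor as experimental or control, so it is the trial arm and not the therapy group. The only covariates named are variables that differ at baseline and, at the follow-up visits, the pre-to-post change.

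The Sample Size section lists a 5% two-tailed alpha, 80% power, a Cohen's d of 0.68 for quality of life and 20% attrition, and arrives at 55 per arm. It gives no ICC and no design effect.

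**The concern.** ANOVA and ANCOVA treat every participant as an independent observation. In the Mind&Life arm, participants spend about 30 hours (15 sessions of 2 hours) with the same peers over the same calendar period. If this makes their outcomes alike, the arm mean varies more than the model assumes. Neither kind of covariate in Section 2.10 represents the therapy group.

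At stake is the arm comparison for every outcome at every post-baseline visit. For any positive within-group correlation, the error runs towards false-positive results. The Discussion expects the regional health service to adopt the intervention if it is found effective, so a false positive would have consequences. The power calculation is exposed as well.

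This is not a detail left to an unseen analysis plan. Section 2.10 names the model and its factor, and they do not fit the delivery in Section 2.4.2.

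**Working it through.** **Inputs from the protocol.** d = 0.68, two-sided alpha 0.05, power 80%, attrition 20%, 55 per arm, therapy groups of 12 to 14. I read d as the standardised difference between arms.

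**Assumed.** ICC 0.01 to 0.10, because the document gives none.

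**The plan's own figure.** A two-sample t-test with these inputs needs 34.9, so 35 evaluable per arm. 35/0.8 = 43.75, so 44 per arm, not 55. The 55 is therefore not reproduced (applying the attrition twice would give it: 35, 44, 55). That is a separate matter. Here it means that 55 × 0.8 = 44 completers per arm are expected, and 44 per arm gives 88% power if all observations are independent.

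**Number of therapy groups.** 55/14 = 3.9 and 55/12 = 4.6, so about 4 to 5. Four groups of up to 14 hold 56. With 44 completers in 4 groups, m = 11.

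**Type I error of the planned test.** Clustering is in one arm only:

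- Design effect in the Mind&Life arm: DE = 1 + (m − 1) × ICC
- True variance over assumed variance of the arm difference: VR = (DE + 1)/2
- Type I error = 2 × [1 − Φ(1.96/√VR)]

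Example at ICC 0.05: DE = 1 + 10 × 0.05 = 1.50; VR = 1.25; √VR = 1.118; type I error = 8.0%.

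| ICC | DE | VR | true SE / planned SE | type I error, formula | type I error, simulated |
|---|---|---|---|---|---|
| 0.01 | 1.10 | 1.05 | 1.025 | 5.6% | 5.5% |
| 0.02 | 1.20 | 1.10 | 1.049 | 6.2% | 6.2% |
| 0.05 | 1.50 | 1.25 | 1.118 | 8.0% | 8.0% |
| 0.10 | 2.00 | 1.50 | 1.225 | 11.0% | 11.1% |

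The simulation used 4 groups of 11 against 44 independent controls. With no dropout (55 per arm, m = 13.75) the formula gives 5.7%, 6.5%, 8.8% and 12.6%.

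**Power of a test that allows for clustering.** The test compares the mean of the 4 therapy-group means with the mean of 44 controls, with Satterthwaite degrees of freedom: df = (v1 + v2)² / [v1²/(4 − 1) + v2²/(44 − 1)], where v1 = DE/44 and v2 = 1/44. At ICC 0.05 this gives about 8 df; at ICC 0, about 11. Simulated power at d = 0.68, without baseline adjustment:

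| ICC | power |
|---|---|
| 0 | 81% |
| 0.01 | 79% |
| 0.02 | 77% |
| 0.05 | 70% |
| 0.10 | 61% |

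The fall from 88% to 81% at ICC 0 comes from having few clusters, not from correlated outcomes.

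**With baseline adjustment.** If baseline explains an assumed 30% of the variance and the ICC applies to the adjusted outcome, power is about 88%, 83% and 74% at ICC 0.02, 0.05 and 0.10. If baseline removes only individual-level variance and leaves the therapy-group component untouched, I obtain about 87%, 79% and 67%.

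**The case against.** The case for a milder reading is substantial, and most of it stands.

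- **Low ICC is plausible.** Session structure and content are fixed (Table 2) and participants have a manual. A reader might infer that shared therapists drive the clustering, but Section 2.4.2 reads as two psychologists responsible for the sessions. If the same pair leads every group, the therapist is constant across the arm and adds no between-group variance. Shared peers and calendar timing remain as sources.
- **The excess over 5% is conditional.** A reader might infer that the type I error certainly and materially exceeds 5%. The document supports this only if the ICC is positive, and the excess is slight at 0.01 to 0.02.
- **The power loss is easily overstated.** Reading the whole drop from 88% to 77%, 70% or 61% as the effect of clustering would be wrong: 7 of those points arise at ICC 0, and baseline adjustment recovers much of the loss. The 88% is also derived; the protocol claims 80%. With a normal approximation instead of Satterthwaite df, power is 88%, 86%, 81% and 74% at ICC 0.01, 0.02, 0.05 and 0.10.
- **Confidence intervals.** Section 2.10 speaks of p-values and Cohen's d, not intervals, so planned intervals cannot be criticised. Any interval built on the same standard error would share the problem.
- **The surplus in 55 per arm.** It cushions power, but does nothing for the type I error. Nothing in the Sample Size section suggests that it was meant as a clustering allowance.
- **The remedy has limits.** Four or five clusters estimate a variance component poorly, and an estimate of zero is common at low ICC. The check above simulated a cluster-mean test, not the mixed model. That test's own type I error was about 5.0% to 5.9%.

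None of this makes a model without a therapy-group term suitable for the design. It limits the size of the problem.

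**Conclusion.** The point holds in conditional form. Delivery is clustered in one arm, the named analysis treats all participants as independent, and the sample size makes no allowance. For any positive within-group correlation the planned test is anti-conservative: slightly at ICC 0.01 to 0.02 (about 5.5% to 6%), materially from 0.05 (about 8%), and about double the nominal level at 0.10 (about 11%).

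A valid unadjusted test falls below the stated 80% power from ICC 0.01 upwards. With baseline adjustment under the 30% assumption, power is above 80% at ICC 0.02, about 79% to 83% at 0.05, and below 80% at 0.10.

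These figures rest on 4 groups of 11 completers, 44 controls, d = 0.68 between arms and an assumed ICC range. The change should be made. It can be made at any time before analysis, provided therapy-group membership is recorded.

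**What to change.** 1. Record each Mind&Life participant's therapy group.
2. In Section 2.10, replace the ANOVA/ANCOVA for the arm comparison with a partially nested mixed model: fixed arm effect, baseline value of the outcome as covariate, random therapy-group effect in the Mind&Life arm only (each TAU participant a cluster of one), residual variance by arm, and Satterthwaite or Kenward-Roger degrees of freedom.
3. State in advance that the therapy-group term stays even if its variance is estimated near zero, or name a cluster-mean Satterthwaite test as a check.
4. Report the ICC, with a note that 4 to 5 groups estimate it imprecisely.
5. Restate power in the Sample Size section over a stated ICC range, for example 0.01 to 0.10, with the assumed baseline correlation.

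Cost: revised wording, one extra variable and a somewhat more complex model. The stated power will be lower, the test less precise and the ICC estimate imprecise. Neither treatment delivery nor randomisation changes.
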